## Abstract

**Background:**

Major depressive disorder (MDD) is a prevalent and severe disorder. Although effective treatments for MDD are available, many patients remain untreated, mainly because of insufficient treatment capacities in the health care system. Resulting waiting periods are often associated with prolonged suffering and impairment as well as a higher risk of chronification. Web-based interventions may help to alleviate these problems. Numerous studies provided evidence for the efficacy of web-based interventions for depression. The aim of this study is to evaluate a new web-based guided self-help intervention (GET.ON-Mood Enhancer-WL) specifically developed for patients waiting to commence inpatient therapy for MDD.

**Methods:**

In a two-armed randomised controlled trial (*n* = 200), the web-based guided intervention GET.ON-Mood Enhancer-WL in addition to treatment as usual (TAU) will be compared with TAU alone. The intervention contains six modules (psycho education, behavioural activation I & II, problem solving I & II, and preparation for subsequent inpatient depression therapy). The participants will be supported by an e-coach, who will provide written feedback after each module. Inclusion criteria include a diagnosis of MDD assessed with a structured clinical interview [SCID] and a waiting period of at least three weeks before start of inpatient treatment. The primary outcome is observer-rated depressive symptom severity (HRSD_24_). Further (explorative) questions include whether remission will be achieved earlier and by more patients during inpatient therapy because of the web-based preparatory intervention.

**Discussion:**

If GET.ON-Mood Enhancer-WL is proven to be effective, patients may start inpatient therapy with reduced depressive symptom severity, ideally leading to higher remission rates, shortened inpatient therapy, reduced costs, and decreased waiting times.

**Trial registration:**

German Clinical Trial Registration (DRKS): DRKS00004708.

## Background

Major depressive disorder (MDD) is one of the most prevalent psychiatric disorders, with a lifetime prevalence that is currently estimated at about 16% [1-3] and predicted to further increase in the foreseeable future [4,5]. By 2030, depressive disorders are anticipated to be responsible for the highest disease burden in high-income countries among all diseases [6]. Suffering from MDD is accompanied by a substantial loss in quality of life, not only for patients but also for their relatives [7-9]. Furthermore, suffering from a depressive episode is associated with a high risk of relapse and recurrence [1,10] as well as a chronic course [11], increased mortality rates [12], significant disability, high medical service use, and major economic costs [13-16].

Although numerous studies provide evidence for the efficacy of available psychological and pharmacological treatments [17,18], many individuals remain untreated [19,20]. The reasons for this treatment gap are twofold. First, individuals who likely to benefit from treatment do not seek treatment because they lack knowledge on available treatment options, anticipate negative (social) consequences, live in underserved areas, fear prohibitive costs, or prefer self-help [20]. Limited availability of clinicians and difficulties in attending therapy during usual business hours are further barriers [21]. Second, those who do seek help rarely receive immediate access to treatment due to long waiting lists for both inpatient and outpatient psychotherapy [20,22]. Consequently, people with an urgent need for therapy are left alone with their burden, which poses several ethical, practical, and therapeutic problems. In addition to high levels of suffering, long waiting times might increase symptom severity and hence increase the need for more intense and longer treatments [23,24].

Another related problem is that because of factors such as limited financial resources and time, inpatient patients are often discharged from the clinic at a very early stage, leaving them with substantial residual symptoms. However, even low levels of residual symptoms are known to increase the risk for relapse and recurrence [25-28]. Recent meta-analyses show that between 40 and 60% of patients with MDD relapse after the initial response to an acute-phase treatment [27].

The use of the internet to provide guided self-help might contribute to solving these problems. First, meta-analytical evidence has shown comparable effects of such interventions compared to traditional psychological treatments when there is at least some support from a professional [29-31]. Furthermore, web-based interventions may represent a far-reaching method for supporting patients during the waiting time for psychotherapy [32].

This method has been well accepted by patients and shown to be effective in the acute treatment phase as well as the maintenance phase [33-37]. The adaptation of internet-based strategies for the waiting phase has several advantages: (a) patients can begin their treatment immediately with no additional waiting time; (b) the online program can be used 24 hours a day, independent of office hours, every day of the week; (c) the material can be reviewed as often as needed; (d) the patient can use it in a familiar environment, without any time or travel costs, which allows for privacy and consistency of care [34,38,39]; and (e) web-based interventions can help patients to practise skills that are relevant for their subsequent therapy (i.e., self-monitoring, problem-solving competencies, behavioural activation).

However, to the best of our knowledge, only one study has evaluated the use of internet-based guided self-help for patients on a waitlist for psychotherapy [40]. In this non-randomised observational study, the researchers found large and significant between-group effect sizes for online treatment for depression (*d* = 0.94) compared to a waiting control group after five weeks. The majority of eligible patients preferred the web-based problem-solving therapy instead of waiting for face-to-face treatment. Participation in this intervention increased the speed of improvement for symptoms of depression during the following therapy [40].

Given the high level of suffering from a depressive episode and the limited availability of psychotherapy resources, new and innovative approaches are needed to address the long waiting times. Using waiting times effectively by providing patients with evidence-based guided self-help methods might result in higher remission rates at the end of inpatient treatment or an earlier remission, thereby reducing costs.

### Trial objectives and purpose

The aim of this multi-centre randomised controlled trial is to evaluate whether a newly developed web-based guided self-help intervention (GET.ON-Mood Enhancer-WL) is effective in reducing depressive symptom severity in patients waiting for inpatient therapy when compared to treatment-as-usual. Moreover, it will be explored whether participants would respond or achieve remission earlier in the course of the subsequent inpatient therapy and would be more likely to be fully remitted at discharge than would controls.

## Methods

### Study design

In this two-armed randomised controlled trial, we will compare GET.ON-Mood Enhancer-WL combined with TAU to TAU alone. The target group will consist of individuals (*n* = 200) who have been referred to inpatient treatment of major depressive disorder by their general practitioner, psychotherapist, or psychiatrist and are awaiting inpatient therapy in one of the German study clinics (Schön Klinik Bad Arolsen/Bad Staffelstein/Bad Bramstedt). The study will be implemented as part of the routine mental health service of the study clinics. Primary and secondary outcome measures will be assessed at baseline, post-treatment (three weeks), at intake for inpatient therapy, weekly during inpatient therapy, and after inpatient therapy. Table 1 gives an overview of the assessments at all planned time points.

**Table 1 T1:** Overview of assessments

**Measure**	**Description**	**Items**	**T**_ **0** _	**T**_ **1** _	**T**_ **2** _	**T**_ **3** _	**T**_ **4** _	**T**_ **5** _	**T**_ **6** _	**T**_ **7** _	**T**_ **8** _	**T**_ **9** _	**T**_ **10** _
			**baseline pre-treatment**	**weekly monitoring**		**post-treatment**	**pre-inpatient therapy**	**weekly monitoring**					**post-inpatient therapy**
SCID	clinical interview, DSM-V criteria		X										
HRSD primary outcome	depressive symptoms, clinician-rated	24	X			X							
QIDS-C	depressive symptoms and severity, clinician-rated	16	X			X							X
PHQ-9	depressive symptoms	9	X	X	X	X	X	X	X	X	X	X	X
Penn State-worry questionnaire–short version	worrying	3	X			X							X
BA-DS–short version	behavioural activation	9	X			X							X
Social problem solving inventory–short version	problem solving	10	X			X							X
EuroQoL	life quality	5	X			X							X
Brief scale for measuring subjective prognosis of gainful employment	subjective prognosis of gainful employment	3	X										
PATHEV	therapy expectations	11	X			X							X
HAQ	help alliance	11	X			X							X

All procedures were approved by the ethics committee at the Philipps University of Marburg in November 2012 (reference number: 2012-37kr). The trial is registered at the German Clinical Trial Register (DRKS00004708).

### Inclusion and exclusion criteria

Patients will be included in this trial when they (a) are awaiting to be treated with routine mental health care at any of the three study centres, (b) are scheduled to have a waiting time of at least three weeks, (c) are 18 years of age or older, (d) meet criteria of a major depressive episode (according to DSM-V criteria), (e) are motivated to actively participate in the self-guided internet intervention to improve their depressive mood during the waiting time, (f) have access to a computer with an internet connection and a valid email address, and (g) return the signed informed consent form.

We will exclude patients with bipolar disorder or acute psychotic symptomatology (according to DSM-V criteria) or patients showing a notable suicidal risk, as assessed during the structured clinical interview.

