### Assessment of eligibility and randomisation

After signing up for further information via the website, prospective participants will receive an email from the research team that includes detailed information about the study. They will be asked to send back an informed consent form via e-mail if they are willing to participate. Patients providing informed consent will be interviewed by telephone to clarify whether they fulfill the inclusion criteria. These structured clinical interviews for DSM disorders (SCID) will be conducted by psychotherapists-in-training who will be weekly supervised by an experienced clinician. Participants providing informed consent, meeting all of the inclusion and none of the exclusion criteria will enter the study. They will be randomly allocated to treatment conditions and complete initial assessment. The allocation will be performed by an independent researcher not otherwise involved in the study using an automated, computer-based random integer generator (randlist). The allocation will be concealed in advance from the participants, researchers involved in recruitment, and inpatient therapists. Patients will be informed that they can withdraw from the study at any time, without any consequences for their subsequent treatment. See Figure 1 for participants’ flow throughout the study.

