### Assessments

Self-report and observer-rated assessments will take place at baseline, post-intervention (three weeks after randomisation), at intake for inpatient treatment, weekly during inpatient therapy, and after completion of inpatient therapy (see Figure 1 and Table 1 for a detailed overview). Self-report data will be collected using a secure web-based assessment system (AES, 256-bit encrypted), and observer-based assessments will be conducted via the telephone by trained interviewers. Observer-rated assessments will be recorded to examine interrater reliability. In cases of disagreement, the two raters will discuss until a consensus is formed, and the rating agreed upon will be used for further analyses. If no agreement is reached after discussion, the assessment will be rated by an experienced diagnostic rater, and this rating will be used for analysis.

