### Primary and secondary outcomes

#### Primary outcome

The primary outcome is depressive symptom severity, as measured by the Hamilton Rating Scale for Depression (HRSD_24_) [51], with assessments conducted pre-and post-treatment. The HRSD is likely the most widely used clinician-rated scale for measuring depression. It assesses depressed mood, vegetative and cognitive symptoms of depression, and anxiety symptoms during the prior seven days. Items are rated on either a five-point or a three-point scale, and the total score is derived by summing the individual item scores. Higher scores indicate greater symptom severity. The HRSD has an interrater-reliability of 0.90 [51] and shows high internal consistency (*α* = 0.88) [52]. Furthermore, it is sensitive to change over time and treatment and corresponds well with overall clinical ratings of severity [53,54]. The cut-off points of 10, 19, 27, and 35 represent the thresholds for mild, moderate, severe, and very severe depression, respectively [52].

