## Discussion

Major depression is a prevalent and severe disorder. Several circumstances lead to the fact that patients remain untreated despite their urgent need for help. Web-based treatments may be an appropriate way of bridging the time gap for patients on a waiting list. Using waiting time efficiently by introducing patients to upcoming therapeutic components before the start of inpatient therapy might be a promising approach to reduce the burden of disease for the patients, to promote earlier discharges and, as a result, to achieve shorter waiting times for subsequent patients.

This study will probably contribute to the literature by evaluating a new web-based intervention for depression compared to treatment as usual in patients on a waiting list for inpatient psychotherapy in a rater-blind randomised controlled trial. We will (a) test the main hypothesis that providing patients access to internet-based, guided self-help will lead to reduced symptom severity before inpatient treatment starts. Moreover, we will (b) investigate whether patients achieve remission earlier and (c) whether we can find significantly more patients with remission or response at the end of inpatient treatment.

There are several strengths to this study: This study will likely be one of the first randomised controlled studies that investigates a web-based intervention for patients on a waiting list for inpatient psychotherapy. We will also (a) use validated clinician-rated measures administered by independent raters blind to treatment condition in addition to self-report, (b) include a specific sample defined by standard diagnostic measures, (c) implement an appropriate statistical analysis plan, and (d) use state-of-the-art methods to cope with missing data.

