This trial has also several limitations: As the trial will be conducted within the context of routine mental health care, the time span between the post-treatment assessment (conducted after the web-based treatment) and the beginning of inpatient therapy depends on both the capacities of the clinic and the eagerness of the patient and therefore will vary between patients. We will assess post-treatment data in both conditions at three weeks after randomisation to ensure a comparable time frame. Hence, patients will be at varying states within the online training when the post-treatment assessment takes place. Furthermore, we chose not to include a placebo/attention control condition because the TAU condition cannot be foreknown and is expected to be quite heterogeneous. Besides it is our aim is to study the effectiveness of GET.ON Mood Enhancer-WL in addition to and compared with usual care, as is standard in pragmatic trials [72]. However, due to the lack of such an active control condition, the mechanisms responsible for any possible effects will remain unclear. Last, we will include follow-up assessments only until the end of inpatient treatment. Therefore, we cannot draw conclusions about the effects on the long-term course of symptoms.

In the long term, it would be a desirable step to increasingly implement a new procedure such as this into the daily routine of inpatient as well as outpatient therapy. It would be good practice for the therapist to know in detail what steps the patient has taken previously and to be able to continue the previous gains. This knowledge would assist both the patient and the therapist, saving time and effort, and allowing them to concentrate on further issues and to intensify the treatment process.

Future research could make use of a homogenous control group, focus on various modifications of the program to identify active ingredients, compare different interventions that are likely to be effective as pre-inpatient treatments, evaluate web-based interventions for other disorders than depression or change the setting into the field of outpatient therapy.

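### The minimum three-week wait leaves no margin before the three-week primary rating, so some primary HRSD ratings can fall on or after admission

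*Protocol article*

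**What the plan says.** - **Eligibility.** Under Inclusion and exclusion criteria, item (b), patients qualify if they "are scheduled to have a waiting time of at least three weeks". The abstract's Methods paragraph gives the end point of that wait ("a waiting period of at least three weeks before start of inpatient treatment"). Neither place gives its start.
- **Timing of T3.** The Assessments section places the post-intervention assessment three weeks after randomisation. The limitations in the Discussion repeat this: "We will assess post-treatment data in both conditions at three weeks after randomisation to ensure a comparable time frame".
- **Primary outcome.** The HRSD is the primary measure, "with assessments conducted pre-and post-treatment". Table 1 marks it at T0 and T3 only. At intake (T4) the only measure marked is the PHQ-9. The HRSD rates symptoms over the previous week ("and anxiety symptoms during the prior seven days").
- **Order of steps.** Under Assessment of eligibility and randomisation, "Patients providing informed consent will be interviewed by telephone to clarify whether they fulfill the inclusion criteria"; allocation follows. No maximum gap between interview and allocation is given.
- **Hypothesis.** The Discussion states that access to the intervention "will lead to reduced symptom severity before inpatient treatment starts". The Interventions section likewise describes the aim as lowering symptoms ahead of intake.
- **Admission date.** The limitations say that the interval from T3 to admission varies with clinic capacity and with how keen the patient is to start.

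**The concern.** The main hypothesis is about the waiting period, so the primary rating has to be made before admission. The wait criterion is the only stated rule that could secure this. Its figure equals the T3 interval, and only the T3 interval is tied to randomisation. A site could follow both rules exactly and still rate some patients on or after admission.

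Once admitted, both arms receive individual and group therapy based on CBT, with medication where needed. With its seven-day look-back, an HRSD rating made after admission describes inpatient days in part or in full. For those patients the rating answers a different question from the one in the hypothesis, and the contrast between arms is probably weaker. As Table 1 has no HRSD at intake, no other primary-outcome rating can stand in.

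**Working it through.** **1. The plan's own sample size.** Inputs from Sample size: d = 0.40, two-sided α = 0.05, power 0.80, N = 200. The allocation ratio is not stated; 1:1 is assumed. The normal approximation gives 99 per arm, 198 in total. The t-test solution is 99.08 per arm, hence 100 per arm and 200 in total, with power 0.804. The stated figure reproduces and has almost no reserve.

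**2. Timeline.** Let W be the scheduled wait in days, L the days from the start of the wait count to randomisation, and T3 = 21 days after randomisation. Then

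inpatient days at T3 = max(0, L + 21 − W).

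The documents give no value for L, so the lags below are assumptions. L = 0 means that the wait is counted from randomisation.

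| W (days) | L = 0 | L = 3 | L = 7 | L = 14 |
|---|---|---|---|---|
| 21 (permitted minimum) | 0 | 3 | 7 | 14 |
| 24 | 0 | 0 | 4 | 11 |
| 28 | 0 | 0 | 0 | 7 |
| 35 | 0 | 0 | 0 | 0 |

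At the permitted minimum and L = 0, T3 and admission fall on the same day. Any earlier start of the count puts T3 after admission by the length of the lag. With a seven-day look-back, min(days, 7) of the 7 rated days are inpatient days: 3 of 7 at a 3-day lag, and all 7 at lags of 7 or 14 days. A patient with a 35-day wait is unaffected at every lag shown, so the problem lies with waits near the minimum and with admissions brought forward.

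**3. Effect on power (illustration).** Let f be the share rated on or after admission and s the share of the effect lost in them. The average effect is

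d = 0.40 × (1 − f × s).

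Power is from the two-sample t-test, 100 per arm, two-sided 0.05. The documents give neither f nor s.

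| f | s | d | Power |
|---|---|---|---|
| 0 | – | 0.40 | 0.80 |
| 5% | half | 0.39 | 0.78 |
| 5% | all | 0.38 | 0.76 |
| 10% | half | 0.38 | 0.76 |
| 10% | all | 0.36 | 0.72 |
| 20% | half | 0.36 | 0.72 |
| 20% | all | 0.32 | 0.61 (0.615) |

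Dropping the affected ratings does not recover the loss: with d kept at 0.40, power is 0.78, 0.76 and 0.71 when 5%, 10% and 20% are set aside. None of these figures includes dropout or any change in variance.

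**4. After the change.** If W is counted from randomisation (L = 0) and must be at least 21 days plus the T3 interview window, inpatient days at T3 are 0 for every patient admitted as scheduled. N stays at 200.

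**The case against.** The best reply is that the intended order is clear. Table 1 puts T3 before intake, and the limitations speak of a span between T3 and admission. A scheduled wait is most naturally the wait still ahead when eligibility is checked. Information and consent come before that interview, so they use up the wait only if it is counted from application, which the article does not say. On the natural reading only the gap from interview to allocation matters. The start of the count and the handling of early admission could be left to the full protocol, which is not shown; nor is the flow diagram.

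Much of this stands. The start of the wait is unstated, and a reader who infers that the protocol counts it from some date other than randomisation goes beyond the text. The intended order is also plain. But the stated criterion does not secure that order: on the most favourable count the margin is zero. The limitations paragraph deals only with variation after T3 and takes it for granted that admission follows. The point therefore rests on rules that the article does state.

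The reply is also right about size. The shares and losses are assumed. Total loss of the effect within days of admission fits poorly with the trial's own expectation that gains carry into inpatient therapy.

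**Conclusion.** The criterion and the T3 timing, as written, allow primary ratings on or after admission, contrary to the hypothesis they are meant to test. This should be corrected, but it is limited in reach. It concerns patients at or near the minimum wait and those admitted early; their share cannot be derived from the documents and may be small. In the milder 10% illustration power falls from 0.80 to about 0.76; the larger losses need stronger assumptions.

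Three stronger readings are tempting and are not supported:

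- **The primary outcome as a whole fails to test the hypothesis.** Patients rated before admission are unaffected.
- **The result is biased in one direction.** Both arms go on to inpatient treatment, so dilution is the likely consequence. Admission timing could in principle differ by arm, because it depends partly on the patient, but nothing in the article shows that it does.
- **The sample size is wrong.** It reproduces on its stated inputs.

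**What to change.** - **Reword criterion (b)** so that the scheduled admission date is at least three weeks, plus the T3 interview window, after the date of randomisation. State the length of that window.
- **Keep all randomised patients in the primary intention-to-treat analysis**, and report by arm how many T3 HRSD ratings were made on or after the day of admission.
- **Treat any analysis that leaves those ratings out as supportive only.** Admission timing is a post-randomisation event, so excluding by it can introduce selection that the primary analysis avoids.

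Moving T3 forward for patients admitted early is not recommended as a routine remedy. It would break the common three-week frame that the article chose on purpose, and those patients would be rated after less exposure to the programme.

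The cost is a change of wording and one extra date check at enrolment. A few patients with very short waits become ineligible; how many cannot be told from the documents. The sample size does not change.
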